### Sample size

An analysis of a number of previous studies of an online intervention for depression in the community and that have used a CBT protocol similar to the intervention in the current study have reported post-treatment effect sizes averaging 1.29, and follow-up effects averaging 1.42, based on samples ranging from 45 – 300
[39,42-48]. We calculated power using G-Power software
[49], using a power of 0.80 and an alpha of 0.05, we would need 60 subjects in each arm of the trial to observe a moderate (*d =* .50) post-treatment difference.

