### Randomization

Randomization will take place at the individual level after the baseline screening. Computer algorithms will determine scores on the screening questionnaires and will automatically assign participants to one of two groups – active intervention group or a waiting-list control group. Participants will be immediately informed about the randomization outcome. The randomization procedure will be managed by a person independent of the research group (Figure 
1).

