### Assessments

Participants will be assessed at baseline, posttreatment, and at 3 and 6 months follow-up. The study variables assessed are summerized in Table 
2.

**Table 2 T2:** Study measures to be used

**Measure**	**Assessment**	**Time of assessment**
Beck Depression Inventory-II (BDI-II)	Depression symptoms	Baseline, posttreatment and follow-up
Generalized Anxiety Disorder-7 (GAD-7)	Anxiety symptoms	Baseline, posttreatment and follow-up
Sociodemographic & History Questionnaire	Gender, age, marital status, education, occupation, socioeconomic status, and history	Baseline
Work and Social Adjustment Scale (WSAS)	Work and Social Adjustment scale	Baseline, posttreatment and follow-up
EuroQol 5D (EQ-5D)	Quality of Life	Baseline, Posttreatment and follow-up
Engagement and Usage data	Engagement and usage	Continuous
Satisfaction with Treatment (SAT)	Satisfaction with therapy	Posttreatment
Helpful and Hindering Aspects of Treatment (HAT)	Helpful and hindering aspects of therapy	After each session

At baseline, assessments include the Beck Depression Inventory-II (BDI-II), Sociodemographic & History Questionnaire, Generalized Anxiety Disorder-7 (GAD-7), and the Work and Social Adjustment Scale (WSAS), and EuroQol 5D (EQ-5D) will be completed for screening purposes. Thereafter the BDI-II, GAD-7, EQ-5D and WSAS will be completed at the end of treatment, week 8, and at follow-up, week 20 (3-months) and week 32 (6-months). After each session participants will be asked to complete the Helpful Aspects of Treatment Form (HAT). The measure Satisfaction with Treatment (SAT) will be administered at week 8.

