### Planned statistical analysis

The analyses will be based on the intention-to-treat principle, including those who began treatment and provided follow-up data irrespective of treatment compliance. Effects will be tested at the 0.05 level. All analyses will be carried out using SPSS. Baseline differences in demographic and clinical characteristics will be investigated using ANOVA. To assess for significant changes over time, repeated measures ANOVAs will be performed for the primary outcome measure for depression (BDI-II). In case of significant time x group interactions, contrasts will be conducted comparing changes from baseline to post-treatment for each group separately. Further any relationships between baseline sociodemographic data and outcomes on the primary outcome measure will be assessed. Repeated measures ANOVAs will also be used to assess any changes over time for secondary outcomes (GAD-7, EQ-5D and WSAS).

The magnitude of the within-group effects of each of the interventions (Cohen’s *d*) will be calculated using the pooled standard deviation. The magnitude of between-group effects will be established by subtracting the Cohen’s *d* statistic for the two groups
[63]. For Cohen’s *d* an effect size of 0.2 to 0.3 can be considered a small effect, around 0.5 a medium effect and 0.8 upwards, a large effect
[64].

Analysis will be made to determine the proportion of participants who make clinically meaningful change at end of treatment and at follow-up. An assessment of *remission* will be made using pre-treatment compared to post-treatment and follow-up scores on the primary outcome measure (BDI-II) and also for the secondary outcomes (GAD-7). The assessment of *remission* will consider the following cut-off scores for the primary outcome measure BDI-II score of <14
[50], and GAD-7 total score ≤8
[57] and and WSAS <10
[59]. In addition, using the post-treatment scores for depression (BDI-II) and anxiety (GAD-7) and dividing these with their pre-treatment scores a calculation of relative risk of depression and anxiety can be made
[58].

An index of *recovery* will be established by identifying the percentage of participants whom achieved a 50% reduction in pre-treatment compared to post-treatment score on BDI-II and GAD-7
[58]. In addition we will also calculate the number of reliably changed and recovered participants using Jacobson and Truax’s
[65] criteria.

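### Baseline differences are to be tested by ANOVA: the p-value is coding-dependent for nominal items and uninformative for all; a descriptive table should replace the tests (minor)

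*Protocol article*

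**What the plan says.** Under Planned statistical analysis, the article states that "Baseline differences in demographic and clinical characteristics will be investigated using ANOVA". One method is named, and it covers demographic and clinical characteristics alike. The same section sets the level: "Effects will be tested at the 0.05 level".

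Table 2, under Assessments, lists what the sociodemographic and history questionnaire records: "Gender, age, marital status, education, occupation, socioeconomic status, and history". The BDI-II, GAD-7, WSAS and EQ-5D are also taken at baseline.

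Under Randomization: "Randomization will take place at the individual level after the baseline screening", and "The randomization procedure will be managed by a person independent of the research group".

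The primary outcome is analysed by repeated measures ANOVA on the BDI-II. If the time-by-group interaction is significant, contrasts of the change from baseline to post-treatment follow within each group.

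**The concern.** There are two separate problems.

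- **Wrong tool for nominal items.** ANOVA compares means of a numeric variable. Marital status and occupation have no natural numbers, so the mean compared is the mean of arbitrary codes, and renumbering the categories changes the p-value.
- **A test without a question.** When individuals are randomised and the arms are compared as randomised, any baseline difference arises by chance. A significant result is then an expected false alarm. A non-significant one does not show that an imbalance is harmless for the BDI-II.

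What is at stake is the baseline table: p-values that cannot be interpreted for some rows, and a sizeable chance that some row is flagged with no stated rule for what follows.

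**Working it through.** **Inputs.** From the article: two arms; 7 items in the Table 2 demographic row plus 4 scales, so 11 characteristics; level 0.05; planned arm size 60 ("we would need 60 subjects in each arm of the trial to observe a moderate" difference, d = 0.50). Assumed for illustration: the category counts in step 1, the independence of tests in step 2, and the correlation r in step 3.

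The plan gives no figure on baseline testing to reproduce. Its one design figure, 60 per arm, does not come out exactly from its stated inputs (two-sided 63 by the normal approximation, 64 by the t distribution; one-sided 50 or 51). Nothing below rests on that; 60 is used only as an arm size.

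**1. Dependence on coding.** Take a four-category nominal item with counts 20/25/10/5 in one arm and 25/12/13/10 in the other.

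- Chi-square: the pooled counts are 45, 37, 23, 15, so half of each is expected per arm. χ² = 2 × (2.5²/22.5 + 6.5²/18.5 + 1.5²/11.5 + 2.5²/7.5) = 7.18 on 3 df, p = 0.066, whatever the numbering.
- ANOVA with codes 2, 4, 3, 1: means 175/60 = 2.92 and 147/60 = 2.45, p = 0.014.
- ANOVA with codes 4, 3, 1, 2: means 175/60 = 2.92 and 169/60 = 2.82, p = 0.63.
- Over all 24 codings, p runs from 0.014 to 0.63, and 8 of the 24 fall below 0.05.

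In a null simulation (4,000 trials, 60 per arm, assumed shares 0.40/0.35/0.15/0.10), each fixed coding rejects in about 5% of trials (0.040 to 0.054). At least one coding is significant in 22% of trials, and the median spread of p across codings is 0.73.

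For a binary item the issue disappears: with 20/40 against 30/30, ANOVA gives 0.0650 and chi-square without continuity correction 0.0641.

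**2. Chance findings under sound randomisation.** P(at least one p < 0.05) = 1 − 0.95^k for k independent tests.

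| k | P(at least one) | Expected number, 0.05k |
|---|---|---|
| 6 | 26% | 0.30 |
| 11 | 43% | 0.55 |
| 15 | 54% | 0.75 |

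The expected number does not need independence; the probability does.

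**3. Precision available from baseline BDI-II.** Between baseline and week 8, the time-by-group interaction is the between-arm comparison of change. With equal SDs σ at both times and correlation r, the variance per participant is 2σ²(1 − r) for change and σ²(1 − r²) for the post-treatment score adjusted for baseline. The ratio is (1 − r²)/[2(1 − r)] = (1 + r)/2: 0.65 at r = 0.3, 0.75 at r = 0.5, 0.85 at r = 0.7.

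**The case against.** The strongest defence is that these tests decide nothing, and that a condensed article commonly leaves the choice of test per variable to the analysis plan. The first part stands and keeps the point minor. The second is weak here, because the article does not leave the method open: it names one, for all characteristics.

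Other parts of the defence also stand:

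- **Few items are clearly affected by coding.** The questionnaire is still to be developed, so response formats are unknown. Age and the scale scores are numeric, gender if binary is harmless, and education or socioeconomic status could be ordinal. Only marital status and occupation are clear cases.
- **The test is not mis-sized.** With a coding fixed in advance, type I error stays near 5%. The p-value is arbitrary, not anti-conservative.
- **The 43% is soft.** The scales are probably correlated with one another, as are education, occupation and socioeconomic status. The history item has several parts and the EQ-5D has two. The range for 6 to 15 tests is the fairer statement.
- **Chance is the only cause just for the arms as randomised.** The section describes an analysis set of those who began treatment and gave follow-up data. In that set differential attrition could also produce imbalance, although a p-value would still be a poor guide to it.

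A reader might infer that these tests are the plan's only handling of baseline imbalance, so that a non-significant difference in baseline BDI-II would be ignored. The article does not support that: baseline BDI-II enters the repeated measures ANOVA as a time level, and the interaction subtracts any baseline difference, significant or not. Nor does it say that a flagged variable would lead to adjustment; it plans, independently of these tests, to look at how sociodemographic data relate to the primary outcome.

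**Conclusion.** The concern holds as a minor point of analysis and reporting. The stated rule gives coding-dependent p-values for nominal items with three or more categories, and tests a hypothesis known to be true for every characteristic compared between the arms as randomised. With 6 to 15 tests, the chance of at least one spurious flag is 26% to 54% if they are independent. The spread of 0.014 to 0.63 rests on assumed counts; the dependence on coding does not.

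No primary or secondary treatment comparison is invalidated. The covariate suggestion is a gain in precision, not the repair of a neglected imbalance. Its size rests on the assumed r and on equal SDs. Because eligibility restricts baseline BDI-II to 14–29, the baseline SD may be the smaller one, and the gain may then differ from (1 + r)/2.

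**What to change.** **Main change.** Replace the sentence on baseline ANOVA with a statement that baseline characteristics will be summarised by arm for all randomised participants, as n (%) for categorical items and mean (SD) for numeric ones, without significance tests. This costs one sentence and is less work than the plan.

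**Separate, optional gain.** Pre-specify the between-arm comparison of week-8 BDI-II with baseline BDI-II as covariate, applied whatever imbalance is seen. This should stand in place of baseline as an outcome level, not alongside it, so that baseline is not used twice. It needs no new data, but it does change the primary model, so it is more than a wording edit and should be settled before outcome data are examined.

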**Method/Design:**

The study is a randomized controlled trial of an online CBT (iCBT) program for the treatment of adults with depressive symptoms. The trial will include an active treatment group and a waiting-list control group. The active condition will consist of 8 weekly modules of iCBT, with post-session feedback support. Participants in the waiting list will receive access to the treatment at week 8. Participants will complete the Beck Depression Inventory (BDI-II) and eligibility criteria will also apply. Primary outcomes are depressive symptoms. Secondary outcomes include quality of life indicators, significant events and satisfaction with online treatment. Data will be collected at baseline and at post-treatment, week 8, and at follow-up week 20 (3-months) and week 32 (6-months). Analysis will be conducted on the intention-to-treat basis.

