#### Waiting list control group

Participants in the waiting-list control group receive no treatment for the duration of the first 8 weeks. At week 8 waiting-list participants will complete the primary and secondary outcome measures (BDI-II, Sociodemographic & History, GAD-7, WSAS and EQ-5D) and will be given access to the program for 8 weeks with support from a trained volunteer.

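### The time-by-group test does not say which visits it uses, although the waiting list is an untreated control only up to week 8

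*Protocol article*

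**What the plan says.** **Schedule.** Under Assessments: "Thereafter the BDI-II, GAD-7, EQ-5D and WSAS will be completed at the end of treatment, week 8, and at follow-up, week 20", with a further assessment at week 32. The section does not distinguish the arms.

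**Control period.** The abstract states: "Participants in the waiting list will receive access to the treatment at week 8". The Waiting list control group section adds that these participants "will be given access to the program for 8 weeks with support from a trained volunteer". They are therefore untreated for weeks 0 to 8 and have the program from about week 8 to week 16.

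**Analysis.** Under Planned statistical analysis: "To assess for significant changes over time, repeated measures ANOVAs will be performed for the primary outcome measure for depression (BDI-II". The next step is: "In case of significant time x group interactions, contrasts will be conducted comparing changes from baseline to post-treatment for each group separately". GAD-7, EQ-5D and WSAS are also to be analysed by repeated measures ANOVA.

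**Sample size.** The target of 60 per arm is set for a standardised difference of 0.50 at post-treatment, with power 0.80 and alpha 0.05.

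**The concern.** The trial's question is whether the program does better than no treatment. Only week 8 can answer it with a randomised, untreated comparator. At week 20 both arms have had access: the active arm is 12 weeks past its treatment period and the waiting list about 4. At week 32 the figures are 24 and 16.

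The analysis section does not tie its between-arm test to week 8. The only such test is an interaction over unnamed visits. The contrasts that do mention baseline and post-treatment look at each arm on its own. A significant change in one arm and not in the other is not a test of the difference between arms.

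Two things are at stake:
- A four-visit interaction can lose power for the week-8 effect, because it spreads the test over three degrees of freedom and includes visits at which the contrast may have shrunk.
- A significant four-visit result does not show at which visit the arms differ.

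**Working it through.** **1. The plan's own figure.** A two-sided two-sample t test with d = 0.50, alpha 0.05 and power 0.80 needs 64 per arm (63 by the normal approximation). At the stated 60 per arm its power is 77.5%. This small shortfall is a separate matter. It matters here only because it shows that the design figure refers to one between-arm difference at post-treatment.

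**2. Time since treatment.** The waiting list finishes at about 8 + 8 = week 16.
- Week 20: 20 − 8 = 12 weeks (active) and 20 − 16 = 4 weeks (waiting list).
- Week 32: 32 − 8 = 24 weeks and 32 − 16 = 16 weeks.

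**3. Power of the interaction.** Let d_j be the standardised arm difference at visit j, with 0 at baseline. Let n = 60 per arm, with equal variances and a common correlation rho between visits. The noncentrality is

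lambda = (n/2) × Σ(d_j − mean d)² / (1 − rho),

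referred to F with k − 1 and (2n − 2)(k − 1) degrees of freedom for k visits. The documents give no rho; 0.5 is assumed, with a range of 0.3 to 0.7.

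At rho = 0.5:
- *Baseline and week 8, d = (0, 0.5).* The mean is 0.25 and the sum of squares 2 × 0.0625 = 0.125. Lambda = 30 × 0.125 / 0.5 = 7.5 on 1 and 118 df.
- *Four visits, half persisting, d = (0, 0.5, 0.25, 0.25).* The mean is 0.25 and the sum of squares again 0.125. Lambda is the same 7.5, now on 3 and 354 df.
- *Four visits, no later difference, d = (0, 0.5, 0, 0).* The mean is 0.125 and the sum of squares 0.140625 + 3 × 0.015625 = 0.1875. Lambda = 11.25 on 3 and 354 df.

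| Visits and pattern | rho 0.3 | rho 0.5 | rho 0.7 |
|---|---|---|---|
| Baseline and week 8, d = 0.5 | 63% | 78% | 94% |
| Four visits, half persisting | 46% | 62% | 85% |
| Four visits, no later difference | 65% | 81% | 96% |
| Four visits, no difference at any visit | 5% | 5% | 5% |

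**4. Does a significant result point to week 8?** With d = 0 at week 8 and 0.3 at both later visits, the four-visit interaction rejects in 47% of trials at rho 0.5 (34% to 71% over the range). This is an illustration and not a forecast. It shows only that the test does not identify the visit.

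**5. Sensitivity to unequal variances.** The entry range of 14 to 29 narrows the baseline spread, so equal variances are doubtful. A simulation of 4,000 trials assumed a baseline SD of 4.5, later SDs of 9 and correlation 0.5, with a Greenhouse-Geisser correction. For a 4.5-point week-8 difference with half persisting, power is about 0.68 for the four-visit interaction and 0.87 for a week-8 ANCOVA. With no later difference the figures are about 0.84 and 0.88. The pattern is the same.

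**The case against.** The strongest reply is that the document never puts weeks 20 and 32 into the model. The only time points named beside the interaction are baseline and post-treatment, the sample size concerns a post-treatment difference, and the hypothesis is about change after the intervention. A two-visit ANOVA fits this text, and its interaction is a proper controlled test of change to week 8. The Waiting list control group section also mentions only a week-8 assessment for controls. If controls are not measured later, a four-visit comparison of the arms cannot be run. This stands: a reader might infer that the model covers all four visits, but the text does not establish it.

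Other stronger readings also fail:
- *The four-visit interaction is an invalid test.* It is not. It keeps its 5% level when the arms do not differ at any visit, and it validly compares immediate with delayed access. It answers a different question from the one the trial was sized for.
- *It would often be significant with no week-8 effect.* That needs a program that does nothing in the active arm by week 8, yet the arms differ after both have had it. This is possible but contrived.
- *Losses at weeks 20 and 32 would cut power sharply.* That rests on a completion rate the documents do not give. Handling of missing visits may sit in an analysis plan not shown.
- *The gate withholds the controlled test.* The gated contrasts are within-arm. The between-arm test is the interaction itself.
- *The sponsor plans between-arm efficacy claims at follow-up.* No such claim is stated.

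A condensed article may leave detail to an analysis plan. This one, however, states the test, the condition and the contrasts, and as written they do not name a between-arm comparison at week 8.

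**Conclusion.** The concern holds in a limited form. The visits in the primary between-arm test are not fixed, and the choice decides whether that test isolates the program's effect against an untreated control. Under a two-visit reading the interaction does so. Under a four-visit reading it does not. Power for the week-8 effect then falls from about 78% to 62% if half of the difference persists, and is about the same (81% against 78%) if none does. These figures assume 60 per arm with complete data, d = 0.5 at week 8, equal variances and correlation 0.5. Over correlations of 0.3 to 0.7 the loss when half persists runs from 63% against 46% to 94% against 85%. The documents do not support saying that the planned test is invalid or certainly includes the later visits.

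**What to change.** Amend Planned statistical analysis to:

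1. Name the between-arm comparison at week 8 as the primary test for BDI-II, and the same comparison for GAD-7, EQ-5D and WSAS. Either a model using baseline and week 8 only or a week-8 between-arm contrast from an all-visit model will serve.
2. Run that comparison without making it conditional on an omnibus interaction, and do not rest the between-arm conclusion on separate within-arm contrasts.
3. State whether waiting-list participants are assessed at weeks 20 and 32. Report those visits as follow-up without an untreated control, with no between-arm effectiveness claim.

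The cost is wording. No visit, measure or participant is added, and no stated claim is given up.

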## Discussion

The study seeks to evaluate the efficacy and effectiveness of an online delivered treatment for depressive symptoms in a sample of adult users of a charity service. The study will be a first contribution to the potential for An online low-intensity intervention to demonstrate decreases in depressive symptoms for participants as compared to the waiting-list control. The study will be a contribution to the already established work in online treatments for depression worldwide.

The primary outcome measure (BDI-II) that will assess depressive symptoms is a well established measure and has been used in other trials of internet-delivered treatments. The secondary outcome measures (GAD-7, HAT, SAT, EQ-5D, WSAS) included in the study will contribute to what participants find satisfying with online treatments and further will detail what in-session events and their impacts participants report as being helpful or hindering in their online treatments. The WSAS will yield information on improvements in quality of life for participants, as will the EQ-5D. The GAD-7 will shed light on the prevalence of comorbid anxiety disorder that occurs with depression in the sample.

It is hoped that with the inclusion of pre-treatment and during treatment dropout questionnaires that the study can make a contribution to developing a better understanding of the reasons for dropout in online treatments.

Depending on the sample recruited the results may be generalizable to people with mild to moderate symptoms of depression in Ireland and may therefore give insight into the potential of low-intensity interventions for Irish people with depressive symptoms. The internet-based intervention is probably most interesting for people who look for alternative healthcare because the possibility of accessing traditional services is near impossible, prohibitive due to waiting lists, costs, and personal stigma.

While the study will not include an official diagnosis of participants, it does include established measures that will gather valuable data on participants that can allow us to begin to build a picture of the relevance of iCBT treatments for depression in Ireland.

